### Plans to promote participant retention and complete follow-up {18b}

Children with hemifacial microsomia and their guardians are concerned about their prognosis since it affects function and appearance. Furthermore, collecting the patients’ contact information, such as their mobile phone number, WeChat ID, and email address, is common practice. Patients are also given our center’s phone number, which they may use to call our medical practitioner if they have any issues. We maintain constant contact with the patients in this manner to ensure proper follow-up. Also, certain patients must return to our facility for additional treatment of compounded issues, such as the occlusal condition. The medical team will give comprehensive pre- and postoperative care to encourage trial participants’ retention. All patients will be followed for 6 months for postoperative recovery and complications, and the PI will review the procedure and respond to the investigator’s report. The Clinical Research Center/Office of Quality Management of Shanghai 9th People’s Hospital, School of Medicine, Shanghai Jiao Tong University, will audit and verify the program’s data every quarter.

### Data management {19}

The image data will be imported into Geomagic Control X (3D System, SC) and Mimics (Materialise, Belgium). The accuracy of the osteotomy will be the primary outcome of the effectiveness of robotic technology. The precision of the osteotomy plane will be assessed by pre- and postoperative CT within 7 days following surgery. Mandibular symmetries will be assessed according to the CT 6 months after the surgery.

This team will provide for doctors to record essential information after surgery during the follow-up period for security indicators such as intraoperative blood loss, operation time, hospital time, any blood transfusion, and rates of complications.

### Confidentiality {27}

Every participant will be allocated an ID number, and their grouping data will be confidential and enveloped. All participants’ personal information will be collected by professional investigators and stored in secure cabinets with limited access. The digital data in the measurement program will be available exclusively via password to the team in charge of measurements.

### Plans for collection, laboratory evaluation, and storage of biological specimens for genetic or molecular analysis in this trial/future use {33}

Not applicable. No biological specimen is needed in this trial.

## Statistical methods

### Statistical methods for primary and secondary outcomes {20a}

The SAS software (version 9.4, SAS Institute, USA) will be used to analyze and process primary and secondary outcomes.* N* (%) and mean ± standard deviation (SD) with median and interquartile range shall describe all quantitative data. If the data follows a normal distribution, we use Student’s* t*-test to compare the two groups. For comparing enumeration data across groups, a sample size of less than 40 necessitates using Fisher’s exact test. *P* < 0.05 is deemed statistically significant.

### Interim analyses {21b}

Not applicable. Given how promptly the study could be conducted, there is little risk of significant complications arising.

### Methods for additional analyses (e.g., subgroup analyses) {20b}

Not applicable. No subgroup analysis will be performed.

### Methods in analysis to handle protocol non-adherence and any statistical methods to handle missing data {20c}

The analysis in this trial will be based on the intention-to-treat (ITT) principle. The ITT will also handle those who meet the withdrawal criteria, including demographic information. If that data is lacking, the statistician will use the last observation carried forward (LOCF) method to finish the analysis.

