### Outcomes {12}

#### Primary outcome

The primary outcome will be the accuracy of osteotomy by comparing the preoperative design and postoperative CT. The two mental foremen and the condylion of the unaffected side are marked as the registration points. Altogether, 10 points on the osteotomy plane of each pre- and postoperative CT scan are selected to calculate the accuracy (Fig. 4a). Each patient’s data will be measured three times to avoid measurement bias, and the staff responsible for measurement are blinded to the patient’s grouping information.

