#### Secondary outcomes

The secondary outcome includes the symmetry of the mandibular, pain scale, recording of surgical complications, and satisfactory score.

The symmetry of the mandibular is evaluated by three indicators: the angle of inclination, the mandibular ramus’s height, and the mandibular body’s length, which will be obtained from the CT 6 months after the surgery (Fig. 4b).

The angle of inclination: A horizontal plane (HP) is established by selecting bilateral suborbital points (Or) and the healthy superior external auditory canal points (Po). Establish the occlusal plane (OP) from the adjacent medial point of the maxillary central incisor to the medial buccal cusp of the bilateral first molar. Measure the angle between the occlusal plane and the horizontal plane, set as angle A. The smaller angle A indicates the smaller deviation angle of the mandible and maxilla, meaning the better symmetry of the lower face.

The height of mandibular ramus: The height of mandibular rami, that is, the distance between condylion (Co) and mandibular gonion (Go), is measured respectively. The distance of the affected side is set as *h*, and the distance of the healthy side is set as *H*. Comparing the values of the affected and the healthy sides. The smaller the difference, the better the bilateral symmetry.

The length of the mandibular body: The menton (me) is marked, and the length of the bilateral mandibular body, the distance from the bilateral gonion (Go) to the menton (Me), is measured respectively. The distance of the affected side is set as *l*, and the distance of the healthy side is set as *L*. Comparing the values of the affected and the healthy sides, the smaller the difference, the better the bilateral symmetry.

The pain scale: The evaluation time is 1 week, 1 month, and 6 months after surgery. The pain scale is an international visual analog scale, with a scale from 0 to 10 representing no pain to the most intense pain.

The postoperative complications during the trial will be recorded, including local infection, bone nonunion, scar hyperplasia, occlusal disorder, nerve injury, and tooth germ injury.

The satisfaction score was evaluated by a modified 5-point Likert table, with 1–5 indicating unsatisfactory to very satisfied. It will be recorded at the 1-week, 1-month, and 6-month follow-up.

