## Data collection and management

### Plans for assessment and collection of outcomes {18a}

The image data from the preoperative and postoperative procedures will be transferred into Geomagic Control X (3D System, SC). The accuracy of the osteotomy plane is assessed after the registration.

The accuracy of the osteotomy between the preoperative plan and the postoperative result will be the primary outcome measure. The postoperative CT will be performed within 7 days following surgery, which is the most critical outcome for determining the efficacy of robotic navigation technology. Improvements in the symmetries of the mandibles will be assessed by comparing the CT 6 months after MDO and the preoperative ones with Mimics.

It will be organized for surgeons to record important information after surgery during the follow-up period for security measures such as intraoperative blood loss, operation time, hospitalization, possible blood transfusion, and complication rates.

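### Last observation carried forward is the only missing-data rule, but the assessment schedule leaves it undefined for the primary outcome and misleading for the 6-month secondary outcomes

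*Protocol article*

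**What the plan says.** The section on non-adherence and missing data (item {20c}) first sets the population: "The analysis in this trial will be based on the intention-to-treat (ITT) principle". It brings in patients who meet the withdrawal criteria, then names one method for gaps: "If that data is lacking, the statistician will use the last observation carried forward (LOCF) method to finish the analysis". The rule is not limited to particular outcomes, and no other method is given.

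The timing of the outcomes is set elsewhere in the article:

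- **Primary outcome section:** "The primary outcome will be the accuracy of osteotomy by comparing the preoperative design and postoperative CT". Item {18a} adds: "The postoperative CT will be performed within 7 days following surgery". Table 1 has a single tick for this outcome, at 7 days.
- **Symmetry (three indicators), Secondary outcomes section:** "which will be obtained from the CT 6 months after the surgery". Table 1 agrees, with one tick at 6 months. Item {18a} describes improvement as "comparing the CT 6 months after MDO and the preoperative ones with Mimics".
- **Pain:** "The evaluation time is 1 week, 1 month, and 6 months after surgery". No preoperative score is scheduled.
- **Satisfaction:** "It will be recorded at the 1-week, 1-month, and 6-month follow-up".

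The sample size section (item {14}) allows for 10% loss to follow-up and enrols 11 patients per group.

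**The concern.** Carrying a value forward needs an earlier measurement of the same quantity, and it is reasonable only if that quantity would have stayed about level. The schedule fails the first condition for the primary outcome. It fails the second for symmetry, which the operation is meant to change, and very probably for pain after surgery.

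Two things are at stake. If a primary value is missing, the stated rule gives no answer, so someone must choose one later, possibly with the results in view. If a 6-month secondary value is missing, the rule does give an answer, but it describes the patient before treatment or early in recovery. With 11 patients per arm, each such value carries one eleventh of the arm mean.

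**Working it through.** **1. The plan's own figure.** Inputs from item {14}: 1.99 and 1.32 mm, alpha 0.05 two-sided, power 0.90, allocation 1:1 (so each inverse allocation fraction is 2). Taking 1.99 as the difference and 1.32 as the SD:

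[(1.960 + 1.282) / (1.99/1.32)]² × (2 + 2) × ½ = 9.246, against 9.24 in the article.

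With 10% loss: 9.246 / 0.90 = 10.27, rounded up to 11 per group. The figure reproduces, and this point does not affect it.

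**2. What the rule has to work with.**

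| Outcome | Scheduled after surgery | Earlier value available if the last one is missing |
|---|---|---|
| Osteotomy accuracy | once, within 7 days | none |
| Symmetry (each of 3 indicators) | once, 6 months | preoperative CT only |
| Pain at 6 months | 1 week, 1 month, 6 months | 1-month score; 1-week score if 1 month is also missing |
| Satisfaction at 6 months | 1 week, 1 month, 6 months | as for pain |

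A missing 1-week pain or satisfaction score has no predecessor either.

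**3. How often it matters.** Expected losses at 10%: 11 × 0.10 = 1.1 per arm and 22 × 0.10 = 2.2 overall. If losses are independent, the chance of at least one is 1 − 0.9²² = 0.90.

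**4. Size, for pain.** The article gives no pain scores, so the fall from 1 week to 6 months is an assumption, taken as 1 to 5 points on the 0–10 scale. Shift in the arm mean = (number of carried 1-week scores / 11) × fall.

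- One carried score: 1/11 = 0.09 to 5/11 = 0.45 points.
- Two carried scores in the same arm: 2/11 = 0.18 to 10/11 = 0.91 points.

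If the 1-month score is carried instead, the relevant quantity is the fall from 1 month to 6 months. The effect on the group comparison depends on which arm loses the patient.

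**5. What is lost by not imputing.** With 10 observed per arm and the plan's own inputs, the standardised shift is (1.99/1.32) × √(10/2) = 3.37. Power is then about 0.92 by the normal approximation and 0.89 by the t-test.

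**The case against.** **The rule may concern demographics only.** The words before it mention demographic information for withdrawn patients, so its scope is loosely worded. That much stands. It does not rescue the rule: the section covers missing data in general, and carrying forward has no meaning for demographics.

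**The primary outcome is little exposed.** This largely stands. The 10% is loss over 6 months of follow-up, and the primary CT comes in the first week. The primary is affected mainly by patients who withdraw or do not complete the operation or the CT. The trial also describes itself as exploratory. These points limit the practical harm, but the stated rule still cannot be carried out for the main comparison.

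**Stronger readings that the documents do not support.**

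- A reader might infer that a missing primary value would be scored as 0 mm, the plan compared with itself. Nothing in the article proposes that; without the postoperative CT there is simply no value.
- A reader might infer that the 1-week pain score always reaches 6 months. It does so only if the 1-month visit is also missed.
- A reader might add the usual criticism that single imputation makes standard errors too small. That is not shown here, since a carried value far from the others can raise the standard error. Even in the unsupported 0 mm case, 10 values with mean 1.99 and SD 1.32 have a standard error of 0.417, and adding one value of 0 gives 0.419.
- Item {11b} mentions only demographic data for patients whose allocated procedure is stopped or modified, including for system malfunction. A reader might infer that primary values will be missing mainly in the navigation arm. The article does not say that their CTs will be omitted.

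**Conclusion.** The concern holds. The only missing-data method in the article conflicts with the article's own schedule: it is undefined for osteotomy accuracy, can only restore the preoperative deformity for symmetry, and replaces 6-month pain and satisfaction with an earlier post-operative score. This is a stated rule that does not work, not a detail left to an analysis plan.

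The numerical harm is modest and falls mainly on the 6-month secondary outcomes. About 2 of 22 patients would be affected at the planned loss rate. The pain shift per carried 1-week score rests on the assumed 1-to-5-point fall. No size can be given for symmetry, because the article reports no preoperative or expected 6-month values, and the direction of any bias between arms cannot be predicted. The expectation that most losses come after day 7 is a judgement from the visit schedule, not a figure in the article.

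**What to change.** Delete the carry-forward sentence from item {20c} and replace it with the following.

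- **Primary and symmetry outcomes:** compare observed values by randomised arm, with no imputation in the main analysis. State openly that this departs from including every withdrawn patient, as the section now promises.
- **Sensitivity analyses:** a best-case and worst-case analysis for missing primary values, and one simple sensitivity analysis for missing symmetry values, both specified before results are seen.
- **Pain and satisfaction:** use all observed visits without carrying values forward, for example in a repeated-measures model. Other methods that use only observed scores would also meet the point.

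The cost is a wording change in one section and a little extra programming. The enrolled number stays at 22. The downside is a slightly smaller analysed number, at a cost in power that the calculation above shows to be small on the plan's own inputs.

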### Plans to give access to the full protocol, participant-level data, and statistical code {31c}

In order to view the entire protocol, please visit https://www.chictr.org.cn/showproj.aspx?proj=38142. After the study results are published, the relevant data and statistical code will be published.

## Oversight and monitoring

### Composition of the coordinating center and trial steering committee {5d}

This is a single-center trial. Skilled investigators on the trial staff handle enrollment, clinical data gathering, digital data measurement, and the surgical team performing the procedure and providing medical care. The trial’s PI will check in with the investigators monthly to hear their progress report and ensure everything is running well. The data and research progress will be reviewed and checked every quarter by the trial steering committee from the Clinical Research Center/Office of Quality Management at Shanghai 9th People’s Hospital, School of Medicine, Shanghai Jiao Tong University.

### Composition of the data monitoring committee, its role, and reporting structure {21a}

Staff and specialists from the Clinical Research Center/Office of Quality Management at Shanghai 9th People’s Hospital, School of Medicine, Shanghai Jiao Tong University, will conduct quarterly audits and reviews of the study data as part of the trial’s data monitoring committee. There are no competing interests.

### Adverse event reporting and harms {22}

The available literature on robotic navigation has documented no adverse outcomes in other surgical procedures. Suppose there are any medical issues in either group throughout the follow-up period. In that case, the team’s clinical doctor will document and treat them before reporting to the ethics committee a week later.

### Frequency and plans for auditing trial conduct {23}

PI will review the procedure and hear the results of this test every month. Data audit and verification of the program will be conducted quarterly by the Clinical Research Center/Office of Quality Management at Shanghai 9th People’s Hospital, School of Medicine, Shanghai Jiao Tong University.

### Plans for communicating important protocol amendments to relevant parties (e.g., trial participants, ethical committees) {25}

The protocol’s revisions will be submitted to the ethics committee for review and approval before implementation.

## Dissemination plans {31a}

Patients’ confidentiality and interests will be safeguarded while the study’s results are shared through scientific publications and conference presentations. Anything that could compromise the blind status of the trial will not be made public until after it has concluded. [name], the PI, will take charge of the publication process and receive credit for his work.

## Discussion

This article describes a randomized controlled experiment that intends to investigate the efficacy of EM robotic navigation for treating HFM. Although MDO is complex, osteotomy requires increased precision and stability to produce desirable functional and attractive results [5]. With the help of a robotic navigation system based on artificial intelligence, surgeons can now have real-time navigation based on a 3D model, combining the best of both worlds. Evidence found that it improves depth perception and hand–eye coordination in various surgical procedures. The trial’s results could pave the way for more widespread use of EM robotic navigation technology in MDO procedures. This research’s sample size is relatively tiny compared to past experimental studies on the use of robotic technology in various types of surgeries; hence, the next step would be to conduct a larger sample size and multi-center trial. Data from this study will be used to refine the trial design necessary to demonstrate navigation’s therapeutic utility and to sustain advances made in MDO for HFM.

## Trial status

Protocol version = 1.1

Date of register = December 16, 2021

Date recruitment began = December 16, 2021.

Estimate completion date = December 2024.

## Abbreviations

HFM: Hemifacial microsomia
TMJ: Temporomandibular joint
MDO: Mandibular distraction osteogenesis
CAD: Computer-aided design
EM: Electromagnetic
MSRS: Maxillofacial surgical robot system
CT: Computed tomography
3D: Three-dimensional
DICOM: Digital Imaging and Communication in Medicine
HP: Horizontal plane
ITT: Intention-to-treat
LOCF: Last observation carried forward
PI: Principal investigator
